### INCLUSION CRITERIA

Adolescents, 13-17 years old that fulfill criteria for NSSI according to clinician-administered non-suicidal self-injury disorder index and have engaged in NSSI during the past month. One parent needs to commit to participate in the parent program.

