## POWER

The sample size of this study was determined based on the observed treatment effects in the uncontrolled pilot study of iERITA (EPN: dnr 2015/1895-31/5). Based on an expected average difference of two self-harming episodes between the groups at post-treatment yields a total sample size of 140 participants with a power of 82% given alpha .05, after the 12-week follow-up. Given an estimated attrition rate of 15%, we aim to include 165 adolescents.

The power refers to a 0.05-level Wald test for the interaction between a binary treatment and linear time in a zero-inflated negative binomial regression model at a 0.05 level. The power was estimated with 200 bootstrap samples. The data for the treated group were obtained by sampling with replacement from the available pilot data. The data for the control group was obtained by adding the difference to the count of a bootstrap sample from the iERITA pilot data on the 25 treated patients.

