## Power and Sample Size

### A Randomized Controlled Trial of Internet-delivered Emotion Regulation Individual Treatment for Adolescents with Non-suicidal Self-injury

[name]

September 15, 2017

Figure 1. Histogram of episodes8 (yellow bars) and predicted probabilities from a zero-inflated negative binomial model (red dots)

[figure not shown]

698     Figure 2. Box plots of the distribution of episodes8 over time in weeks

[figure not shown]

699

700

701 Figure 3. Estimated trend of the rate of episodes8 over time with a zero-inflated negative binomial model.

[figure not shown]

702

703

704

Table 1. Estimated power to detect a different slope between the treated and control groups corresponding to different sample sizes and differences in the expected count between groups after the 12-week follow-up. The power refers to a 0.05-level Wald test for the interaction between a binary treatment and linear time in a zero-inflated negative binomial regression model at a 0.05 level. The power was estimated with 200 bootstrap samples. The data for the treated group were obtained by sampling with replacement from available pilot data from an earlier study on 25 treated patients. The data for the control group was obtained by adding the difference specified in the table to the count of a bootstrap sample from the pilot data on the 25 treated patients.

| Difference
between groups
in average count
after 12 weeks | Sample size
per group | Estimated
power |
|--------------------------------------------------------------------|--------------------------|--------------------|
| 1                                                                  | 150                      | 0.80               |
| 2                                                                  | 70                       | 0.82               |

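### The 82% power does not establish the power of this design: simulated controls are treated-pilot counts plus a constant, with no zeros and the treated arm's variance

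*Protocol*

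**What the plan says.** The POWER section assumes "an expected average difference of two self-harming episodes between the groups at post-treatment" and reports "a total sample size of 140 participants with a power of 82% given alpha .05". With 15% attrition the target becomes 165.

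The test is described thus: "The power refers to a 0.05-level Wald test for the interaction between a binary treatment and linear time", in a zero-inflated negative binomial regression, with power estimated from 200 bootstrap samples. The treated arm is resampled from the 25 patients of the iERITA pilot. For controls: "The data for the control group was obtained by adding the difference to the count of a bootstrap sample from the iERITA pilot data". The legend of Table 1, in the appended Power and Sample Size document, repeats the method: "The data for the control group was obtained by adding the difference specified in the table to the count of a bootstrap sample".

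Table 1 gives power 0.80 for a difference of 1 with 150 per group, and 0.82 for a difference of 2 with 70 per group. It labels the difference as applying after 12 weeks. Neither place says at which weeks the constant was added to the simulated counts.

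On eligibility, INCLUSION CRITERIA requires that adolescents meet criteria for NSSI and "have engaged in NSSI during the past month". PRIMARY ANALYSIS uses weekly reports of NSSI frequency.

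**The concern.** Adding a constant to resampled counts does two things that need no assumption to demonstrate. It sets a floor: with a constant of 2, the smallest possible control count is 2. And it raises the mean without raising the variance. A negative binomial arm behaves differently: its variance grows with its mean, and zeros remain possible. The simulated controls therefore could not have come from the model fitted to them. Nor do they resemble the expected patients. Entry requires NSSI only within the past month and the outcome is weekly, so weeks without an episode are to be expected under treatment as usual.

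There is also a timing problem. Read literally, the constant goes on every count, which puts a gap of 2 between the arms at baseline. Randomisation rules this out in expectation.

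The 82% is the protocol's only justification for 140 participants. If it describes an alternative that cannot occur, a null result will be judged against a power that nobody has established.

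**Working it through.** **Reproducing the plan's figures.** The attrition step reproduces: 140 / 0.85 = 164.7, so 165. The 82% cannot be reproduced, because the pilot counts are not in the text. Its Monte Carlo error with 200 samples is sqrt(0.82 × 0.18 / 200) = 2.7 points, so simulation noise alone gives about 77% to 87%.

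**What the shift does.** If Y is a treated count with mean m and variance V, then Y + 2 has mean m + 2, variance V and minimum 2.

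**Reading A: 2 added at every week.** As an illustration, let the treated mean fall from 3 to 1 (assumed). Controls then go from 5 to 3. Both arms fall by 2 episodes, so on the count scale there is no difference in change. On the log scale the interaction is ln[(3/5) / (1/3)] = ln 1.8 = 0.59, produced only by the log link. With equal baselines and the same week-12 gap, controls would stay at 3 and the interaction would be ln[(3/3) / (1/3)] = ln 3 = 1.10. The every-week shift can thus make the tested effect smaller than the intended one.

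**Reading B: the difference builds up to 2 at week 12.** Compare the log rates at that one time point with equal group sizes. By the delta method, the squared standard error is proportional to the sum over arms of variance / mean². Put V = m + αm² (negative binomial).

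- Shifted control: S = V/m² + V/(m+2)²
- Negative binomial control with the same mean: N = V/m² + 1/(m+2) + α
- Ratio of standard errors: r = sqrt(N/S)
- Power of 82% at two-sided 0.05 corresponds to 1.960 + 0.915 = 2.875. The power after the change is Φ(2.875/r − 1.960).

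Example with m = 0.5 and α = 0.5: V = 0.625, S = 2.5 + 0.1 = 2.6, N = 2.5 + 0.4 + 0.5 = 3.4, r = 1.144, power Φ(0.554) = 71%.

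Results, with m and α assumed because the text gives neither:

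| m | α = 0.5 | α = 1 | α = 2 | α = 4 |
|---|---|---|---|---|
| 0.5 | 71% | 68% | 64% | 61% |
| 1 | 68% | 65% | 62% | 60% |
| 2 | 68% | 66% | 65% | 64% |
| 4 | 71% | 70% | 69% | 69% |

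**Simulation check of direction.** Settings: 70 per arm, weekly counts for weeks 0 to 12, a zero-inflated negative binomial with group, time and group × time, a patient-clustered Wald test, and 200 replicates. There were five assumed settings: mean 3 or 4 falling to between 1 and 2, structural zeros 30 to 40%, between-patient dispersion 1 to 2. Shifted arms were resampled from simulated pools of 25. The comparison arm was drawn from the model, with equal baseline and a week-12 mean 2 higher.

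| Control arm | Power in the five settings |
|---|---|
| Drawn from the model | 0.995, 0.845, 0.64, 0.575, 0.885 |
| +2 at every week | 0.855, 0.67, 0.33, 0.365, 0.725 |
| Building up to +2 by week 12 | 1.00, 0.955, 0.855, 0.875, 0.965 |
| +2 in the last week only | 0.67, 0.575, 0.295, 0.25, 0.545 |

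Against the model-based arm, the every-week shift understated power by 14 to 31 points. The last-week shift also understated it in all five settings. The gradual shift overstated it by up to 30 points. Week-12 zeros were 60 to 73% in the treated arm, 0% in shifted controls and 48 to 63% in model-based controls. The model-based control variance was about 3 to 8 times the treated variance (for example 34.8 against 4.3).

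A second set of simulations, with patient-level random intercepts and slopes and a rate-scaled control arm, agrees on the gradual shift: 77 to 85% against 46 to 67% in seven settings chosen so that the shift landed near 82%. For the every-week shift it is mixed: 0.63, 0.65, 0.48 and 0.49 against 0.46, 0.49, 0.67 and 0.62.

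**The case against.** The strongest defence is that the protocol states its alternative and method openly, and that nobody without the pilot data can say the 82% is wrong. That stands. A reader might infer that the trial is underpowered, or that the true power is well below 82%. The documents do not support this. The sign of the error depends on the weeks at which the constant was added, which are not given. Only the gradual build-up consistently overstates power, and neither POWER nor the Table 1 legend describes a gradual build-up. It is one way to read the label of a difference after 12 weeks.

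Three further limits are fair. First, the appended figures (a histogram with fitted probabilities, box plots by week and a fitted trend) are not visible here, so the pilot's zero share and spread may be shown in the source; the values above are assumptions. Second, the size under Reading B is easily exaggerated. Giving both arms the same coefficient of variation yields about 55 to 69%, but that drops the 1/mean term from the negative binomial variance; keeping it gives 60 to 71%. Third, PRIMARY ANALYSIS plans an unspecified count regression with a contrast four weeks after treatment. None of these calculations is therefore the power of the planned primary test.

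Entry also requires NSSI criteria on a clinician-administered index, so participants are not minimal cases. That makes zero weeks less frequent, but not absent, and it does not supply a reason for a floor of 2.

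**Conclusion.** The point holds in a limited form. The missing zeros and the unchanged variance follow directly from the stated method, wherever the constant was added. No reading rescues the 82%. An every-week shift tests an artefact of the log link on arms that differ at baseline, and the figure may then be too low. A shift that builds up to week 12 overstates power, with 82% becoming about 60 to 71% under the assumed means and dispersions (each 0.5 to 4) in a one-time-point approximation that ignores zero inflation and repeated measures. A last-week-only shift understated power in the settings tried.

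The conclusion is therefore that the 82% does not establish the power of this design. It is not that power is known to be lower. The same applies to the 0.80 in the other row of Table 1, where the constant is 1 and the floor is 1.

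**What to change.** 1. State in POWER and in the Table 1 legend at which weeks the difference was added to the control counts.
2. Rerun the simulation with arms equal at baseline and the stated mean difference at post-treatment. Draw control counts from the fitted zero-inflated negative binomial, or scale each resampled patient's rate, so that zeros and dispersion are kept.
3. Replace the 82% in POWER and both rows of Table 1 with the results, whichever direction they move, and state the rate ratio that 2 episodes represents.

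This takes about a day of work. Enrolment can stay at 165 and no extra patients are needed. The downside is that the stated power may become less favourable.

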## PROCEDURE

The study will be hosted by the research clinic of the Child and Adolescent Mental Health care (BUP-CPF) in Stockholm. This unit is a collaboration between CAHMS and Centre for Psychiatry Research (Centrum för psykiatrforskning). Three CAHMS over the country will be hosting the participants.

Adolescents with repeated NSSI, and their parents, will receive information about the study through information directed to CAMHS, primary health care specialized for child and adolescents with psychiatric problems, the school health care, and newspaper and social media advertisement. There are three ways in which the family can be recruited to the study: (1) if the adolescent and his/her parents have contact with a clinician and show preliminary interest in participating in the study, the treating clinician can send a letter of referral to one of the hosting units; (2) the parents can notify interest to participate in the study through self-referral; (3) clinicians at the hosting units recommend families to the designated contact at that unit. In either case, a clinician in the research group or at one of the hosting units, will call the adolescent and parents and examine overall inclusion/exclusion criteria. If it is apparent that the participant does not fulfill inclusion criteria (e.g. has not engaged in repeated NSSI), or fulfills exclusion criteria, the participant will not be invited to the assessment interview. If the youth is in need of some other kind treatment, he/she will receive advice and/or referral to adequate treatment. If the adolescent currently fulfills inclusion criteria, he/she is instructed to log on to a secure website and complete four weekly assessments. These assessments include questions regarding NSSI, other self-destructive behaviors, emotions regulation and attachment. The purpose of these assessments is to confirm that the adolescent is actively engaging in self-harm behavior and to establish a baseline measurement of NSSI severity. After the fourth assessment, the adolescent and his/her parents will undergo a structured face-to-face assessment by a clinician experienced in assessing and treating adolescents with self-harm behavior and suicidal ideation. This includes an assessment of the adolescents' mental health status and the inclusion/exclusion criteria consisting of evaluation of psychiatric comorbidity and suicidal ideation (MINI-KID and BDDQ), borderline personality disorder (SCID-II BPD), functional impairment (CGAS), self-harm behaviors as well as presence or absence of the Nonsuicidal self-injury diagnosis (CANDI). In addition to these

measures, questions about the adolescents' home and school situation will be asked. The adolescent will also get recommendation/referral to other adequate treatment, based on the assessment, independent of ongoing treatment or not.

If a participant and/or his/her parents are not interested in participating, the routines for regular care will be followed (i.e. if the adolescent is not eligible for inclusion the family will be informed about the reasons for exclusion and the participant will receive adequate advice or referral).

Families eligible for inclusion into the study will be informed about the study in a way that is easy to understand for the participant and his/her parents and the right to not participate will be stressed. Participants and parents will be given both verbal and written information about the study, in which the details of the study are outlined and the contact information of the research group is presented, to enable direct contact with the researchers by telephone or e-mail.

When the adolescent is less than 15 years of age, written informed consent will be required from both adolescent's caregivers (if there are two) as well as verbal consent from the adolescent. If the adolescent is over 15 years of age and assessed as being adequately mature (i.e. at expected level of a 15-year old or older) only the parent that participates in the parent program is required to give written informed consent regarding his/her own participation. In these cases, the adolescent provides written informed consent.

If the adolescent and parent(s) consent to participation, they will receive information on how to log on to a secure website comprising pre-assessment and information on demographic variables for both the adolescent and his/her parents. Once the pre-assessment is completed, randomization is executed. The family could either be allocated to starting treatment immediately or start treatment 24 weeks later (when the intervention group has completed the three month follow-up). The treatment lasts for twelve weeks. Both groups are asked to undergo the post-assessment approximately twelve weeks after the pre-assessment. The post-assessment could either be done face-to-face, or via telephone. The follow-up measures at three, six, and twelve months are done via the phone. All assessments are done by the treating clinician (psychologists, psychologists under training or psychotherapists); the post- and follow-up measures are conducted by independent assessors.

#### PRE-, POST AND FOLLOW-UP ASSESSMENTS FOR THE ADOLESCENTS

The pre- and post-assessments includes the structured clinician administrated assessment of the adolescent's functional impairment (CGAS), NSSI (CANDI and DSHI-Y), emotion dysregulation (DERS and DERS-16), borderline personality disorder symptomatology (BPFS-C) and other self-destructive behaviors (BSL-Supl), suicidal ideation (SIQ-JR), accepting stance (AAQ-2), depression, anxiety and stress (DASS-21), and client satisfaction (CSQ). At post and follow-up assessments questions regarding potential adverse events will be addressed (Adverse events). In addition to these scales the therapist will rate participant adherence during treatment (iiPAS).

Weekly measures will be administered four weeks before the face-to-face assessment, during treatment, and four weeks after treatment termination. Four weekly measures will also be administered at each follow-up. The weekly measures consist of four short self-report scales that measure emotion regulation (DERS-16), NSSI (DSHI-Y), other self-destructive behaviors (BSL-Supl), and attachment (ECR-RC). In addition to these scales the participant will be asked to report if there have been any changes in medication during the past week. At treatment week 1, treatment expectancy/credibility (CEQ) will be rated, and therapeutic alliance (WAI) will be rated at week 4. The participants will answer a maximum of 58 questions per week. For a measurement chart, see figure 1.

323

[figure not shown]

324

325 *Figure 1. Chart over the different assessments and measures for both the intervention and waitlist*  
326 *group.*

327

328 PRE-, POST- AND FOLLOW-UP ASSESSMENTS FOR THE PARENTS

329 Parents will complete questionnaires about their own possible history of NSSI (SITBI-SF-SH), and  
330 about how they cope with their child's negative emotions (CCNES-A). At post, questions regarding  
331 potential adverse events will be addressed (Adverse events).

332 PRELIMINARY RESULTS

333 As a first step in evaluating the feasibility, acceptability, and utility iERITA for adolescents with  
334 repeated NSSI, the research group has conducted an open pilot study including 25 adolescents with  
335 NSSID, aged 13-17 years (EPN dnr 2015/1895-31/5). To date, all adolescents have completed  
336 treatment, 24 participants have provided post-treatment data and so far, 19, and 15 participants,

respectively have completed the three- and six-month follow-up assessments. Preliminary analyses reveal statistically significant large effects on NSSI (standardized mean difference between pre- and post-treatment,  $d = 0.88$ ), and moderate effects on emotion dysregulation ( $d = 0.77$ ). At six-month follow-up, these improvements were either maintained or further improved upon, from pre-treatment with statistically significant large effects on NSSI (standardized mean difference between pre- and six-month follow-up,  $d = 1.28$ ), and emotion dysregulation ( $d = 0.92$ ). Ratings of treatment satisfaction, treatment credibility/expectancy and number of completed modules (median = 11; IQR=9-11) were high. No adverse events directly related to the treatment have been reported.

The research group has also interviewed a sub-sample of the participants ( $N = 8$ ; dnr 2015/1895-31/5) about their experience of internet-delivered ERITA. Preliminary results of the qualitative analysis revealed three themes associated with the experience of iERITA: utility, support, and flexibility. Overall, a positive treatment experience was described. What was perceived as useful differed between participants, emphasizing the need of a broad treatment outline. Support was experienced as sufficient and the therapist's contribution was described as necessary for a positive experience. Further, the flexibility of the treatment format was experienced as both positive and negative. A high flexibility could, for some, put a lot of pressure on organization and responsibility, which was described as burdensome. On the other hand, the high flexibility made it easier for the participants to adjust the treatment work to other obligations and was time-saving. These findings were considered when the treatment manual was revised.

#### STATISTICAL ANALYSES

Treatment effects will be evaluated according to the intention-to-treat principle. Primary end-point for all outcomes is post-treatment. Secondary end-point include a controlled 3 month follow-up.

#### PRIMARY ANALYSIS

The primary outcome analysis will include treatment group (ERITA , TAU) and weekly reports of NSSI frequency measured once every week 4 weeks prior to treatment start, once every week during treatment, and once every week four weeks after treatment termination. Regression analysis modelled for count data will be used to estimate trend over time. Four weeks after treatment termination will be considered primary endpoint. Pairwise contrasts (group x time interaction) from the regression model will be used to evaluate between-group differences at primary endpoint (4 weeks after treatment termination).

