#### MEASURES

Data, in the form of self-assessments, will be collected for all participants at baseline (weekly for four weeks) preceding the face-to-face assessment, pre-treatment, weekly during treatment, post-treatment, weekly for four weeks after treatment termination, and weekly for four weeks at three-months follow-up. Additional follow-up for participants that are randomized to iERITA will be collected 12 months after treatment is terminated (see attached flow diagram). Thenceforth, the participants will be offered the possibility to answer the same measures once every year for five years. Assessments are administered via the Internet and answers (also results of the clinical interviews) are securely stored on a database developed for this purpose and have been used in several completed and ongoing studies (dnr: 2011/1816 31/1, 2010/1993-31/4, 2011/2027-31/5, 2012/1995-31/1, 2013/1321-31/3, 2014/1-31/3, 2014/673-31/2; 2014/1885-31, 2015/1722-31, 2015/1895-31/5, and 2015/969-31). All data traffic is encrypted (2048 bit SSL) ensuring a high security level.

---

 The term "parents" refers to legal guardian(s) of the adolescent.

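### One trend is fitted through pre-randomisation, treatment and post-treatment weeks; if time is linear, as in the power section, the primary contrast can misstate the endpoint effect in either direction

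*Protocol*

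**What the plan says.** **Data window.** Protocol, PRIMARY ANALYSIS, enters "weekly reports of NSSI frequency measured once every week 4 weeks prior to treatment start, once every week during treatment" and then "once every week four weeks after treatment termination". With twelve weeks of treatment (PROCEDURE) that is 4 + 12 + 4 = 20 weekly reports per adolescent.

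**Model.** "Regression analysis modelled for count data will be used to estimate trend over time". No break is stated at treatment start or end, and the section does not say whether time is linear or categorical.

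**Endpoint and test.** "Four weeks after treatment termination will be considered primary endpoint", and "Pairwise contrasts (group x time interaction) from the regression model will be used to evaluate between-group differences at primary endpoint".

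**Form of time.** The only one in the document is in POWER, repeated above Table 1 of the Power and Sample Size appendix: a Wald test for the "interaction between a binary treatment and linear time in a zero-inflated negative binomial regression model". The appendix describes this as detecting a difference in slope.

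**Randomisation.** MEASURES places the baseline reports at "baseline (weekly for four weeks) preceding the face-to-face assessment". PROCEDURE puts randomisation later still, once the pre-assessment is complete. All four baseline reports are therefore pre-randomisation.

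**Other endpoint statements.** STATISTICAL ANALYSES gives post-treatment as the primary endpoint for every outcome, and POWER places its planning difference at post-treatment, after 12 weeks. Neither matches four weeks after treatment.

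**The concern.** The three phases differ in kind. Before randomisation the arms cannot truly differ. During treatment the effect builds. Afterwards it may hold, grow or fade. One straight line per arm has no room for these changes: the four pre-randomisation reports help to set each arm's slope, and whatever divergence is fitted must continue at the same rate after week 12.

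The contrast at week 16 is then largely a statement about the whole course. If the real course bends, the primary estimate can miss the difference in the very weeks the endpoint names, and the trial's main conclusion rests on that estimate.

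There is a second problem. PRIMARY ANALYSIS uses a group-by-time interaction as if it were the between-group difference at a given week. With a linear time term these are two quantities with two tests.

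**Working it through.** **1. The plan's own figures.** Table 1 of the appendix gives 70 per group for a difference of 2, so 2 × 70 = 140. Inflating for 15% attrition, 140 / 0.85 = 164.7, rounded up to 165, which reproduces the target. The 82% power cannot be reproduced because the data on the 25 pilot patients are not given. Its simulation error with 200 samples is √(0.82 × 0.18 / 200) = 0.027, a 95% range of about 77% to 87%. That figure is for the linear slope test.

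**2. Slope versus endpoint difference.** Write the linear model as log rate = a + b·G + c·t + d·G·t, with G = 1 for iERITA and t in weeks from treatment start.

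- Slope test: d = 0.
- Log rate ratio at the endpoint: b + 16d.

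The tests coincide only if b = 0, that is, if the fitted lines meet at t = 0. Randomisation makes the true difference zero there, but the model does not impose it, and a bent course pulls b away from zero.

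**3. What one line returns at week 16.** Large-sample check: Poisson log-linear fit to noiseless expected counts, weeks −3 to 16 (4 before, 12 during, 4 after). Assumed, not in the document: control flat at 2 per week, and an effect path on the log scale with full-effect rate ratio (RR) 0.4 (0.6 in brackets). In the first five rows that RR is reached by the end of treatment; in the last two it is the value at week 16. The piecewise model has breaks at treatment start and end.

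| Assumed course | True RR, week 16 | One line | Piecewise |
|---|---|---|---|
| Ramp to week 12, then plateau | 0.40 (0.60) | 0.35 (0.55) | 0.40 (0.60) |
| Early response, then plateau | 0.40 (0.60) | 0.29 (0.51) | 0.44 (0.63) |
| Ramp, then half lost | 0.63 (0.77) | 0.42 (0.62) | 0.63 (0.77) |
| Ramp, then fully lost | 1.00 (1.00) | 0.54 (0.70) | 1.00 (1.00) |
| Ramp continuing to week 16 | 0.29 (0.51) | 0.31 (0.52) | 0.29 (0.51) |
| Onset at week 6, then plateau | 0.40 (0.60) | 0.42 (0.61) | 0.36 (0.57) |
| Onset at week 6, gain to week 16 | 0.40 (0.60) | 0.52 (0.68) | 0.38 (0.58) |

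**4. Sensitivity to distribution and control course.** The linear model was refitted with a full-effect RR of 0.50, as Poisson and as negative binomial (dispersion 1.5), with flat, declining and fall-after-entry control courses:

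- Step, or ramp to week 6 or 12, then held (true 0.50): fitted 0.36 to 0.45. On the log scale, ln 0.45 / ln 0.50 = 1.15 and ln 0.36 / ln 0.50 = 1.47, so the effect is overstated by about 15% to 47%.
- Half lost by week 16 (true 0.71): fitted 0.50 to 0.53.
- Fully lost by week 16 (true 1.00): fitted 0.59 to 0.63.
- Onset at week 6 with gain to week 16 (true 0.50): fitted 0.58 to 0.63. Here ln 0.58 / ln 0.50 = 0.79 and ln 0.63 / ln 0.50 = 0.67, so the effect is understated by about 21% to 33%.
- No effect in any week: fitted 1.00 throughout.

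**5. Is equal baseline enough?** No. With the flat control and RR 0.4, a straight line whose arms are forced equal up to treatment start still gives 0.33 for the ramp and plateau (true 0.40) and 0.51 for the fully lost effect (true 1.00). Time after randomisation must be freed as well.

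**The case against.** The strongest reply is that PRIMARY ANALYSIS never says linear. Pairwise contrasts at a named time fit categorical time just as well, linear time appears only in the power calculation, and knots or random effects are properly left to a statistical analysis plan. This stands in part: the finding is conditional on linear time. It does not dispose of the point. The protocol itself states the pooled window, the trend and the interaction as the endpoint test, and its sample size rests on a linear slope test. If categorical time was intended, the power refers to a different test from the primary one.

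A reader might go further in several ways that the document does not support:

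- *The contrast is an extrapolation.* Week 16 is the last observed week, so it is a fitted value at the edge of the data.
- *The effect is overstated.* The direction depends on the course. Late continuing gain is understated, steady gain to week 16 is nearly unbiased, and a null effect is unbiased.
- *Relapse is likely and will go unseen.* The uncontrolled pilot (PRELIMINARY RESULTS) reports gains held or extended, with d = 0.88 at post-treatment and 1.28 at six months. Lasting relapse could also show in the planned between-group analysis at three months, though that would not correct the primary contrast.
- *Weekly rows are treated as independent, or the test uses only the count part of a zero-inflated model.* PRIMARY ANALYSIS commits to neither.
- *The endpoint was chosen to show durability.* The protocol gives no reason for it.

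Including pre-randomisation reports as repeated outcomes is also legitimate. The difficulty is a single line through them without a break.

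**Conclusion.** The point holds in conditional form. If time enters as one linear term, the primary contrast is driven by earlier weeks and by the assumed shape, and it can misstate the week-16 effect either way. The case that matters most is a transient effect: fully gone by week 16, it would still be reported as a rate ratio of about 0.6. A plain plateau, with no relapse, is already enough to exaggerate the effect.

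These sizes rest on assumed control rates, effect sizes and time courses, none of which the document supplies, and on large-sample fits without noise. They show what the method can do; they do not predict this trial's result.

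Two parts do not depend on the assumed courses. Under linear time the slope interaction and the endpoint difference are different quantities, and the endpoint is worded differently in POWER, STATISTICAL ANALYSES and PRIMARY ANALYSIS.

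**What to change.** In PRIMARY ANALYSIS:

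1. Treat the four pre-randomisation reports as baseline, either as a covariate or as outcomes with the arms constrained equal before randomisation.
2. Model post-randomisation time by phase or by week, or piecewise with breaks at treatment start and end. By phase or by week is safer: the piecewise fit also missed when the course bent within treatment (for example 0.36 against a true 0.40 with onset at week 6 and a plateau).
3. Define the primary test as the between-group rate ratio over the four post-treatment reports, allowing for repeated measures within adolescent. State that this is an average over weeks 13 to 16. For the ramp to 0.4 that is fully lost by week 16, this average is 0.73, while week 16 alone is 1.00.
4. Keep the linear slope as a supportive analysis.

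Then align POWER, STATISTICAL ANALYSES and PRIMARY ANALYSIS on one endpoint and one test.

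**Cost.** Only wording changes, since all the reports are already scheduled. The standard error will be somewhat larger than under a forced straight line, and the 82% power, which belongs to the linear slope test, must be restated for the new contrast.
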